#### 6.3.4 Assessment of causality

The clinical investigator is obliged to assess the relationship between investigational product and the occurrence of each AE/SAE. The investigator will use clinical judgement to determine the relationship. Alternative causes, such as natural history of the underlying diseases, concomitant therapy, other risk factors and the temporal relationship of the event to the investigational product will be considered and investigated. The investigator will also consult the Investigator Brochure and/or Product Information, for marketed products, in the determination of his/her assessment.

There may be situations when a SAE has occurred and the investigator has minimal information to include in the initial report. However, it is very important that the investigator always makes an assessment of causality for every event prior to transmission of the SAE Report Form to AMANET. The investigator may change his/her opinion of causality in light of follow-up information, amending the SAE Report Form accordingly. The causality assessment is one of the criteria used when determining regulatory reporting requirements.

In case of concomitant administration of multiple vaccines, it may not be possible to determine the causal relationship of general AEs to the individual vaccines administered. The investigator should, therefore, assess whether the AE could be causally related to vaccination rather than to the individual vaccines.

All solicited local (injection site) reactions will be considered causally related to vaccination. Causality of all other AEs should be assessed by the investigator using the following question:

*"Is there a reasonable possibility that the AE may have been caused by the investigational product?"*

**NO:** The AE is not causally related to administration of the study vaccine(s). There are other, more likely causes, and administration of the study vaccine(s) is not suspected to have contributed to the AE.

**YES:** There is a possible or probable cause that the vaccine(s) contributed to the AE.

Non-serious and serious AE's will be evaluated as two distinct events. If an event meets the criteria to be determined "serious" (see definition of serious adverse event), it will be examined by the investigator to the extent to be able to determine ALL contributing factors applicable to each serious adverse event.

Other possible contributors include:

- Medical history
- Other medication
- Protocol required procedure
- Other procedure not required by the protocol
- Lack of efficacy of the vaccine(s), if applicable

[figure not shown]

- Erroneous administration
- Other cause (specify)

### **6.3.5 Medically attended visits**

For each solicited and unsolicited symptom the subject experiences, the subject will be asked if they received medical attention defined as hospitalisation, an emergency room visit or a visit to or from medical personnel (medical doctor) for any reason and this information will be recorded in the CRF.

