| Serology Schedule             | D0, D28, D56, D84, and D365                                                                                                                                                                                                                                                                                                                                                                                                                                                                                                                                                                                                                                                                                                                                                                                                                                                                                                                                                                                                                                         |
| Primary Evaluation Criteria   | 
The safety profile will be assessed on the following criteria:
 
 
- Immediate reactogenicity (reactions within 30 minutes after each injection, with emphasis on allergic reaction).
 
- Local and systemic reactogenicity measured from Day 0 to Day 14 after each dose.
 
- Any adverse event resulting in a visit to a physician between each injection and one month after the third dose.
 
- Any Serious Adverse Event (SAE) occurring from inclusion and through out the study. The relationship of the adverse event to the study vaccine will be established by the investigator, using the following definitions : related, or not related
 
- Biological safety: one month after each vaccination, in reference with the baseline before the first dose, by measuring the following: 
 
▪ RBC, haemoglobin, haematocrit, platelets, and WBC.
 
▪ ASAT, ALAT, total bilirubin, alkaline phosphatase, creatinine.
 
 
 
 |

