## 2 OBJECTIVES

### 2.1 Primary Objective

**To evaluate the safety and reactogenicity** of three doses of 30 and 100µg GMZ2, adsorbed on aluminium hydroxide, in comparison with three doses of the control vaccine (rabies), in healthy Gabonese children aged 1-5 years. This will be done through evaluation of the following:

1. Immediate reactogenicity; defined as any systemic adverse reactions occurring within 30 minutes after each injection,
2. Local and systemic reactogenicity measured from Day 0 to Day 14 after each dose,
3. Any unsolicited Adverse Event resulting in a visit to a physician between each injection and one month after the third dose,
4. Any Serious Adverse Event (SAE) occurring from the inclusion throughout the study.

Biological safety, one month after each vaccination, in reference with the baseline level the following :

1. RBC, haemoglobin, haematocrit, platelets and WBCs
2. Creatinine, ASAT, ALAT, total bilirubin and alkaline phosphatase.

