#### 3.1 Overview

- Randomized, controlled, double-blind phase I study
- One trial centre
- Safety oversight by a Safety Committee
- Study monitoring by AMANET
- Screening will be done within 14 days prior to the first vaccination
- Vaccination schedule will be on study days 0, 28 +/- 3, and 56 +/- 3
- Route of administration will be intramuscular on the deltoid muscle, alternately starting with the left side.
- Study duration will be approximately 13 months per participant
- Each participant will attend 16 standardised visits at the trial centre (Inclusion visit D-14; D0; D1; D3; D7; D14; D28; D29; D31; D35; D42; D56; D57, D70, D84, D365).
- Blood samples will be taken by venopuncture at five time points at D-14; D0; D28; D56; D84, and D365. Biological parameters and serological will be assessed at these time points as well as serological parameters. A maximum total of 7.5 mL blood will be taken at each blood sampling. For each participant a maximum of about 37.5 mL blood will be taken during the whole study.
- Twenty four hours, 3 days, 7 days and 14 days after each vaccination a visit is planned to monitor adverse events at D1, D3, D7, D14, D29, D31, D35, D42, D56, D57, D 59, D63 and D70
- Follow-up of serious adverse events (SAEs) until resolution
- The primary analysis will be conducted for all primary and secondary endpoints at a data-lock-point one month post vaccination 3 (study Day 84), after which the Primary

[figure not shown]

Study Report will be produced. These results will be used to decide on the go criteria for the next trial in children.

- The study will then continue in a single-blind fashion. Data gathered during this period will be reported in an addendum report.
- At the end of the study participants will be informed which vaccine they received and those who received malaria vaccine will be offered immunization with the rabies vaccine.

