## 5.5 Unscheduled Visits

Participants will be advised to report to the MRU anytime they feel unwell, regardless of their perceived cause. At such unscheduled visits, a history and physical examination, clinical laboratory tests including malaria smear if indicated, documentation of any AEs, and any other medically indicated diagnostic or therapeutic procedures will be done. These will be recorded as observations in the participant's study record and if the physician finds them to be adverse events, the appropriate CRF sections will be completed.

[figure not shown]

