### 6.3.2 Safety Data Collection

All the Adverse Events, whether observed by the Clinical Investigator or by the parent/guardian of the participant, will be carefully and accurately documented in the CRF by the Clinical Investigator. For each event/reaction the following details will be recorded:

1. Description of the event(s)/reaction(s),
2. Date and time of occurrence,
3. Duration,
4. Intensity,
5. Relationship with the vaccine,
6. Action taken, including treatment,
7. Outcome.

Safety assessments will be obtained and recorded by the Investigator. He/She will not know which vaccine formulation the subject has received. "Solicited" and "unsolicited" reactions/events will be actively followed during 30 minutes after each injection, and during the following 14 days. The table below summarizes the solicited local and systemic reactions that will be sought after and how intensity will be graded.

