## 7 EVALUATION CRITERIA

### 7.1 Primary Evaluation Criterion: Safety

#### 7.1.1 Definition of the Criterion

The safety profile will be assessed on the following criteria:

- Immediate reactogenicity (reactions within 30 minutes after each injection),
- Local and systemic reactogenicity measured from Day 0 to Day 14 after each dose
- Any unsolicited adverse event resulting in a visit to a physician between each injection and one month after the third dose.
- Any Serious Adverse Event (SAE) occurring from the inclusion through out the study. The relationship of the adverse event to the study vaccine will be established by the investigator, using the following definitions: related or not related.
- Biological safety, one month after each vaccination, in reference with the baseline before the first dose, by measuring the following:
  - RBC, haemoglobin, haematocrit, platelets, total WBC;
  - serum creatinine, ASAT, ALAT, total bilirubin, alkaline phosphatase.

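### The component of physician visits for adverse events is scoped two ways, and the CRF item behind it (6.3.5) does not capture visits caused by the event

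*Protocol*

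**What the plan says.** The component appears three times in the Protocol:

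- Synopsis, Primary Evaluation Criteria: "Any adverse event resulting in a visit to a physician between each injection and one month after the third dose".
- Section 2.1, Primary Objective: "Any unsolicited Adverse Event resulting in a visit to a physician between each injection and one month after the third dose".
- Section 7.1.1, Definition of the Criterion: "Any unsolicited adverse event resulting in a visit to a physician between each injection and one month after the third dose".

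Medical attention is defined only in section 6.3.5, as an item recorded in the CRF. It opens "For each solicited and unsolicited symptom the subject experiences, the subject will be asked if they received medical attention" and continues with the definition "medical attention defined as hospitalisation, an emergency room visit or a visit to or from medical personnel (medical doctor) for any reason".

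Three other places bear on how that item would work in practice. On scheduled attendance, section 3.1 says "Twenty four hours, 3 days, 7 days and 14 days after each vaccination a visit is planned to monitor adverse events", and the flow chart adds clinic visits on Days 28, 56 and 84. On who assesses, section 6.3.2 says "Safety assessments will be obtained and recorded by the Investigator". On unscheduled attendance, section 5.5 says "Participants will be advised to report to the MRU anytime they feel unwell, regardless of their perceived cause".

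No section says how the 6.3.5 item is turned into the primary component.

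**The concern.** There are two separate problems.

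The first is scope. Solicited reactions are inside the component in the synopsis and outside it in 2.1 and 7.1.1. Take a solicited fever two days after a dose for which the guardian takes the child to a doctor. The synopsis counts it and the other two sections do not.

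The second is capture. The component asks for events that cause a physician visit. The CRF item asks whether there was a doctor contact, whatever the reason, and does not set aside visits that would have happened anyway. Take a three-day runny nose that spans the scheduled Day 14 visit, with no care sought. It does not meet the component, yet the guardian could properly answer yes to the item if a doctor saw the child that day.

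Incidence of adverse events with 95% confidence intervals by group is a planned output (synopsis, Statistical Methods). The Day 84 analysis feeds the decision on the next trial (3.1 and 8.7.1). A later analysis plan can redefine a flag, but it may not be able to separate care sought for an event from routine attendance if the CRF recorded both as the same yes.

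**Working it through.** The protocol gives no expected rate for this component, so there is no stated figure to reproduce. The check compares the texts and then sizes the loose reading.

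**Scope**

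| Place | Events eligible | Link to the visit |
|---|---|---|
| Synopsis | all adverse events | event leads to the visit |
| 2.1 | unsolicited only | event leads to the visit |
| 7.1.1 | unsolicited only | event leads to the visit |
| 6.3.5 (CRF item) | asked of solicited and unsolicited | any reason |

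The contradiction is between the first row and the next two. The fourth row describes data collection. Its breadth does not contradict an unsolicited-only component, because collected data can be subset. Its missing causal link is the second problem.

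**Size of the loose reading**

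Inputs from the documents: clinic visits 1, 3, 7 and 14 days after each dose (3.1) and again at 28 days (flow chart). The visit list in 3.1 omits Days 59 and 63, which the flow chart includes, so the flow chart is used.

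Assumptions, none of them in the documents: onset uniform over the 28 days after a dose, a fixed duration of d days, visits on their nominal days, a doctor at each scheduled visit, and no care sought.

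The visits cut the 28 days into gaps g of 1, 2, 4, 7 and 14 days. An event that starts within a gap is still present at the visit closing that gap if at most d days remain. So

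share flagged = [min(d,1) + min(d,2) + min(d,4) + min(d,7) + min(d,14)] / 28

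| d (days) | Sum | Share |
|---|---|---|
| 1 | 1+1+1+1+1 = 5 | 5/28 = 17.9% |
| 2 | 1+2+2+2+2 = 9 | 9/28 = 32.1% |
| 3 | 1+2+3+3+3 = 12 | 12/28 = 42.9% |
| 5 | 1+2+4+5+5 = 17 | 17/28 = 60.7% |
| 7 | 1+2+4+7+7 = 21 | 21/28 = 75.0% |
| 14 | 1+2+4+7+14 = 28 | 28/28 = 100% |

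A second count used whole onset days from Day 0 to Day 83 and the 15 post-dose clinic visits from Day 1 to Day 84. It gives 16.7%, 32.1%, 42.9%, 60.7%, 75.0% and 100% for the same durations.

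Under the causal wording shared by the synopsis, 2.1 and 7.1.1, a visit fixed in advance is not caused by the event. The share added by the schedule is then 0% at every duration.

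**The case against.** The strongest reply is that the component already contains the causal link, in all three statements of it, and that 6.3.5 only says what guardians are asked. This is correct. A reader might infer that routine visits automatically make ordinary events medically attended and that the component is therefore inflated. The documents do not support that, because nothing says that a yes to the 6.3.5 item equals the component. Inflation is a risk that arises if the item is used to derive it.

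Several further points also stand:

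- The item is put symptom by symptom, so it can be read as asking about attention for that symptom.
- 6.3.5 requires a medical doctor, and the visit descriptions do not say that one attends every scheduled visit. The percentages above are therefore at the upper end.
- They are shares of events, not of children, and depend on assumed onset and duration.
- Section 5.5 documents unscheduled visits to the research unit separately, so illness-prompted contact there may be recoverable from the study record. The protocol does not say that the component is taken from that source, and 5.5 covers attendance at the research unit only.

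A reader might also infer that the wording pushes all arms to a ceiling and hides a difference between GMZ2 and rabies vaccine. The protocol states no event rate from which a ceiling could be shown. Section 8.6 makes the analysis descriptive, with no comparison between groups, because of the sample size. Outcome assessors are blinded and the schedule is common to all arms, so no direction of bias follows.

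Finally, mapping a CRF item to an analysis flag is often left to the analysis plan. That would answer a plain omission. It does not answer a scope stated two ways, or an item whose any-reason wording conflicts with the link the component needs.

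**Conclusion.** Two things are established: the synopsis disagrees with 2.1 and 7.1.1 on whether solicited events count, and the 6.3.5 item does not implement the causal condition that all three statements of the component contain.

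The effect of the second depends on use. If the item defines the component and scheduled visits are accepted as medical attention, the schedule alone would flag about 18% of 1-day, 43% of 3-day and 75% of 7-day events under the assumptions listed. If the component's own wording governs, it flags none. The documents do not settle which applies.

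The consequence is reduced interpretability of a descriptive safety output. Bias between arms is not shown. The sample size (10 per arm, chosen without a power calculation) and the only stated test, on serious adverse reactions in 8.6.1, are unaffected. Severity: minor.

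**What to change.** 1. In 6.3.5 and on the CRF, replace the any-reason clause with an unscheduled hospital, emergency or physician contact sought because of that event. State that protocol-scheduled clinic visits and field-worker visits do not count.
2. State in 6.3.5 or 7.1.1 that this item defines the third primary component.
3. Add the word *unsolicited* to the synopsis, to match 2.1 and 7.1.1. Solicited reactions already have their own primary component, so none are lost from the safety report.

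The cost is a rewritten definition, one linking sentence, one CRF question and one word in the synopsis. The downside is a lower count of medically attended events. The change is best made before data collection, since a distinction not recorded on the CRF may not be recoverable later.

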### **6.3.6 Follow-up of adverse events and serious adverse events and assessment of outcome**

After the initial AE/SAE report, the investigator is required to proactively follow each subject and provide further information to AMANET on the subject's condition. All AEs and SAEs documented at a previous visit/contact and designated as not recovered/not resolved or recovering/resolving will be specifically reviewed at subsequent visits/contacts.

Investigators will follow-up participants with SAEs or participants withdrawn from the study as a result of an AE, until the event has resolved, subsided, stabilized, disappeared, the event is otherwise explained, or the subject is lost to follow-up; or, in the case of other non-serious AEs, until they complete the study or they are lost to follow-up.

Clinically significant laboratory abnormalities will be followed up until they have returned to normal, or a satisfactory explanation has been provided. Additional information (including but not limited to laboratory results) relative to the subsequent course of such an abnormality noted for any subject must be made available to the Study Monitor.

AMANET may request that the investigator perform or arrange for the conduct of supplemental measurements and/or evaluations to elucidate as fully as possible the nature and/or causality of the AE or SAE. The investigator is obliged to assist. If a participant dies during participation in the study or during a recognized follow-up period, AMANET will be provided with a copy of any available post-mortem findings, including histopathology.

New or updated information will be recorded on the originally completed SAE Report Form, with all changes signed and dated by the investigator. The updated SAE report form should be resent to AMANET within 48 hours of receipt of the follow-up information.

Outcome of any non-serious AE occurring within 30 days post-vaccination (i.e. unsolicited AE) or any SAE reported during the entire study will be assessed and classified as:

1. Recovered/resolved
2. Not recovered/not resolved
3. Recovering/resolving
4. Recovered with sequelae/resolved with sequelae
5. Fatal (SAEs only)

### **6.3.7 Reporting of Serious Adverse Events**

#### **A. Timeframes for reporting of SAEs**

SAEs will be reported promptly once the investigator determines that the event meets the protocol definition of an SAE. The investigator or designate will report to the Study Contact for Serious Adverse Event Reporting WITHIN 24 HOURS OF HIS/HER BECOMING AWARE OF THESE EVENTS. Additional or follow-up information relating to the initial SAE report is also to be reported to the Study Contact for Serious Adverse Event Reporting within 24 hours of receipt of

[figure not shown]

such information. The reporting should be principally by phone; then the investigator should immediately send the **completed SAE report** to AMANET alternatively by email or fax sending it with an acknowledgment of receipt.

#### **B. Completion and transmission of serious adverse event reports**

Once an investigator becomes aware that an SAE has occurred in a study subject, he will report the information to Study Contact for reporting SAEs within 24 hours. The SAE Report Form must always be completed as thoroughly as possible with all available details of the event, signed by the investigator (or designee). If the investigator does not have all information regarding an SAE, he/she will not wait to receive additional information before notifying Study Contact of the event and completing the form. The form will be updated when additional information is received and forwarded WITHIN 24 HOURS.

The investigator must always provide an assessment of causality at the time of the initial report as earlier described.

Initial notification via the telephone does not replace the need for the investigator to complete and sign the SAE Report Form within 24 hours.

In the event of a death determined by the investigator to be related to vaccination, sending of the fax must be accompanied by telephone call to the Study Contact for Reporting SAEs

| Study Contact for Reporting SAEs to AMANET                                                                                                                                                                         |
|---------------------------------------------------------------------------------------------------------------------------------------------------------------------------------------------------------------------------|
| Name, address: [name]
[contact]
[contact]
Outside office hours
Mobile [contact]
Email : [contact] |

#### **6.3.8 Regulatory reporting requirements for serious adverse events**

The investigator will promptly report all SAEs to AMANET in accordance with the procedures detailed above. AMANET has a legal responsibility to promptly notify, as appropriate, both the local regulatory authority and other regulatory agencies about the safety of a product under clinical investigation. Prompt notification of SAEs by the investigator to the Study Contact for Reporting SAEs is essential so that legal obligations and ethical responsibilities towards the safety of other subjects are met.

The investigator, or responsible person according to local requirements, will comply with the applicable local regulatory requirements related to the reporting of SAEs to regulatory authorities and the IRB/IEC.

Expedited Investigator Safety Report (EISR) is prepared according to AMANET/EMVI internal policies and forwarded to investigators when necessary. An EISR is required for:

- Development compounds (i.e. compounds not marketed), if the event is serious, unexpected and has a suspected relationship to study drug treatment.
- If the expected adverse events for development compounds will be described in the Development Core Safety Information (DCSI) in the Investigator Brochure (IB).

The purpose of the EISR is to fulfil specific regulatory and ICH-GCP requirements, regarding the product under investigation.

[figure not shown]

An investigator who receives an EISR describing a SAE or other specific safety information from EMVI will file it with the Investigator Brochure and will notify the IRB/IEC, if appropriate according to local requirements.

